### Strategies to improve adherence to interventions {11c}

The study coordinator is present during the intervention to ensure adherence to the allocation. As the intervention is administered at a single time point during surgery, no further strategies for intervention adherence are necessary.

### Relevant concomitant care permitted or prohibited during the trial {11d}

Patients with radiotherapy or chemotherapy scheduled within 7 days after the surgery are excluded. All other forms of treatment are permitted; however, patients are not allowed to participate in other clinical studies with investigational drugs or devices.

### Provisions for post-trial care {30}

In accordance with the Belgian Law relating to experiments on human persons (May 7, 2004), the sponsor shall assume, even without fault, the responsibility for any damages incurred by a study patient and linked directly or indirectly to the participation to the study and shall provide compensation therefore through its insurance.

## Outcomes {12}

The primary endpoint is the success rate of both techniques, which means the absence of a clinically relevant CSF leak at 12 weeks after surgery, i.e., any leak that needs surgical revision or any other intervention, e.g., puncture or aspiration, longer hospitalization, or repeat imaging. The success rate in both groups will be reported in proportions with a 95% confidence interval.

Secondary endpoints include an analysis of peri- and postoperative complications (CSF leakage, both clinically relevant (incisional leakage) and not clinically relevant (swelling, pseudomeningocele), surgical site infection and treatment-site bleeding in particular), as well as a cost-effectiveness evaluation. In addition, the study will compare the efficiency of L-PRF in supratentorial and infratentorial surgery, based on surgical approach and technique.

Peri- and postoperative complications will be obtained from the hospital databases. Each complication requiring additional treatment (surgical revision, intervention, or drug therapy) or investigation (clinical or imaging) or which requires or prolongs hospitalization will be considered. RAND SF-36 questionnaires will be filled out preoperatively (baseline) and 6–12 weeks post-surgery to evaluate patient-reported health concepts such as physical functioning, bodily pain, role limitations due to physical health problems, role limitations due to personal or emotional problems, emotional well-being, social functioning, energy/fatigue, and general health perceptions. The questionnaire is scored as indicated on the official website of RAND, adapted from the scoring described by Ware and Sherbourne [10]. The difference in the change in score to baseline will be compared between the groups, i.e., treated with commercially available fibrin sealants or treated with L-PRF.

For the cost-effectiveness analysis, the “healthcare payer” perspective will be adopted, which means that all direct treatment-related costs as well as costs related to follow-up will be included in the analysis. For the cost analysis, the following outcomes will be considered: used materials during surgery (units), surgery duration (minutes), intensive care hospitalization time (days/hours), duration of hospitalization (days), associated facility, and staff resources. These data will mainly be retrieved from the hospital records and requested at the hospital’s billing office, if necessary. The most recent unit prices at the time of analysis will be applied. Depending on the primary outcome, i.e., the effectiveness of dural closure, and the clinical effects of both treatments, analysis will be performed as cost-utility or as cost minimization [11, 12]. In addition, the use of EQ-5D-3L to calculate QALYs at 6–12 weeks postoperative will be explored to compare EQ-5D utility scores to other outcomes described above.

The outcomes will be assessed at five study visits within a timeframe of twelve postoperative weeks (Table 2), and a comparison will be made between the two groups considering the change to baseline. Data will be presented as mean and standard deviation or median and interquartile range for continuous variables (including body temperature, °C; blood pressure, mmHg; diameter of craniotomy, mm) and as proportions with 95% confidence intervals for categorical variables (complications, surgical indication, surgical approach). Baseline medical characteristics will be compared between the allocation groups in a similar fashion.

**Table 2 Tab2:** Outcome assessment

Procedure	Visit 1: *screening*	Visit 2: *allocation*	Visit 3: *FU1*^a^	Visit 4: *FU 2*^b^	Visit 5: *FU 3*^c^

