**Methods/design:**

This single-blinded, prospective randomized controlled interventional trial aims to demonstrate the non-inferiority of L-PRF compared to commercially available fibrin sealants for dural closure. This trial will include patients undergoing cranial neurosurgery (supratentorial and infratentorial) with intentional opening of the dura. Patients are randomized in a 1:1 fashion comparing L-PRF to commercially available fibrin sealants. The primary endpoint is postoperative CSF leakage within 12 weeks after surgery. Secondary endpoints are complications such as bleeding or wound infections. Additionally, a cost-effectiveness analysis is performed.

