**Fig. 2 Fig2:**
[figure not shown]
Flowchart of “L-PRF in cranial surgery, a prospective randomized controlled trial.” After obtaining informed consent, patients are screened and asked to complete quality of life (QoL) questionnaires (EQ-5D and RAND SF-36). During surgery (i.e., before dural closure), study subjects are randomized into the experimental arm (L-PRF) and the control arm (commercially available fibrin sealants). During hospitalization, patients are followed up with clinical controls after 2 days (FU1) and on the day of discharge (FU2). One outpatient follow-up is done between 6 and 12 weeks postop (FU3), with MRI imaging and completion of the QoL questionnaires

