**Assessments**					
Medical history	X				
EQ-5D	X				X
RAND SF-36	X				X
MR imaging	X				X
Cost/material registration		X			
CSF leakage assessment			X	X	X
Wound healing assessment			X	X	X
Infection assessment			X	X	X
Adverse events		X	X	X	X

*FU* follow up

^a^Two days postoperative

^b^At hospital discharge

^c^Six to twelve weeks postoperative

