#### Outpatient follow-up

At 6–12 weeks (FU3), the patient is seen at the outpatient department for another examination of the surgical site. CSF leakage, infection, and wound healing are assessed. Medication use is recorded, and EQ-5D and RAND SF-36 questionnaires are completed. Postoperative imaging is performed.

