#### Procedure for unblinding if needed {17b}

Unblinding may be done after completion of the outpatient follow-up visit (FU3) or in case of any serious adverse event that is probably related to the study.

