#### Data management {19}

Data are collected partially on paper source documents (patient questionnaires) and electronic source documents (patient medical records containing surgical and hospitalization reports, registration of used materials). Data is collected by the principal investigator or his designee and locally entered into the e-CRF (RedCap). RedCap is primarily a data collection tool to facilitate post-study analysis based on qualitative data. Access to the e-CRF is strictly regulated and only possible with personal credentials obtained only after successfully completing a specific examination. All data operations are monitored and verified via a tracking system. Entries are verified by double entry (for example manual and automated summary of EQ-5D result); format checks, e.g., integer; and warning messages if data are outside an expected range of values.

As appropriate, baseline characteristics will be reported by mean and standard deviation or number and proportions. The effect of the intervention on the primary outcome will be assessed by comparing the proportion of patients presenting with a postoperative CSF leakage within 12 weeks after surgery.

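### The primary endpoint runs to 12 weeks, but the last scheduled leak assessment may fall at week 6 and unblinding is allowed from then, so late leaks may be missed

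*Protocol article*

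**What the plan says.** **Endpoint horizon.** Outcomes {12} defines success as "the absence of a clinically relevant CSF leak at 12 weeks after surgery" and explains a relevant leak as one that needs revision, another intervention, a longer stay or repeat imaging. The Abstract (Methods/design) states: "The primary endpoint is postoperative CSF leakage within 12 weeks after surgery". Data management {19} describes the analysis as "comparing the proportion of patients presenting with a postoperative CSF leakage within 12 weeks after surgery".

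**Assessment schedule.** Table 2 lists CSF leakage assessment at day 2 (FU1), discharge (FU2) and FU3, and its footnote gives FU3 as "Six to twelve weeks postoperative". The caption of Fig. 2 reads "One outpatient follow-up is done between 6 and 12 weeks postop (FU3". At this visit, according to the Outpatient follow-up paragraph of {13}, "CSF leakage, infection, and wound healing are assessed". FU3 is the fifth and last study visit. If it is missed or falls outside its window, {18b} provides a telephone call, but only for the questionnaires.

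**Other sources.** Outcomes {12}, in the paragraph after the secondary endpoints, adds: "Peri- and postoperative complications will be obtained from the hospital databases". No end date is given for that search. Section {20c} expects no missing data for the primary endpoint.

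**Unblinding.** Section {17b} states: "Unblinding may be done after completion of the outpatient follow-up visit (FU3".

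**The concern.** The endpoint window and the observation window differ. A patient examined at week 6 still has six of the twelve endpoint weeks ahead, with no planned contact to ask about a leak. A patient examined at week 12 has none. The length of scheduled observation therefore depends on when the appointment was booked, although both patients are reported as 12-week outcomes.

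In a non-inferiority trial on the risk-difference scale, this error is not conservative. If the same share of leaks is missed in both arms, both leak rates fall in proportion and so does the absolute difference. A truly worse treatment then looks closer to the comparator, while the 5-point margin stays fixed. Few events are expected, so a handful of missed leaks would matter.

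The unblinding rule adds to this. Part of the endpoint consists of actions such as repeat imaging or intervention. For a patient seen early, allocation may be released while such actions can still create an endpoint event.

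**Working it through.** **1. The windows side by side.** The endpoint closes at week 12, which is 12 × 7 = day 84. The earliest FU3 is week 6, or day 42. The longest interval without a scheduled assessment is 84 − 42 = 42 days, half of the endpoint window. Unblinding is permitted throughout that interval.

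**2. The plan's own sample size.** Inputs from Sample size {14}: control success 0.937, L-PRF success 0.95, margin 0.05, one-sided alpha 0.05, power 80%. With unpooled variance:

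n per arm = (1.645 + 0.842)² × (0.937 × 0.063 + 0.95 × 0.05) / (0.05 + 0.013)² = 166

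This gives 332 in total, against 334 stated. Power with 167 per arm is 80.2%. The stated figure reproduces, and nothing in this point changes it.

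**3. Expected events.** At 167 per arm, control leaks are 167 × 0.063 = 10.5 and L-PRF leaks are 167 × 0.05 = 8.35.

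**4. Effect of missed leaks.** Take the boundary of the null hypothesis: control leak rate 6.3%, L-PRF leak rate 6.3 + 5.0 = 11.3%. Let f be the share of all leaks that occur after FU3 *and* are not captured by any source, equal in both arms. The documents give no value for f, so 5 to 20% is an assumed range.

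- Observed leak rates: 0.063(1 − f) and 0.113(1 − f)
- Observed deficit: 0.05(1 − f)
- SE = √[(sum over arms of leak rate × (1 − leak rate)) / 167]
- Probability of declaring non-inferiority = Φ((0.05 − observed deficit)/SE − z), with z = 1.645 for one-sided 5%, the alpha in {14}, or z = 1.96 for the two-sided 95% interval in {20a}

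| f (assumed) | Observed deficit, points | Error, one-sided 5% | Error, two-sided 95% interval |
|---|---|---|---|
| 0% | 5.00 | 5.0% | 2.5% |
| 5% | 4.75 | 5.9% | 3.0% |
| 10% | 4.50 | 7.0% | 3.7% |
| 20% | 4.00 | 9.9% | 5.5% |

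Worked line for f = 10%: the leak rates become 0.0567 and 0.1017. SE = √[(0.0567 × 0.9433 + 0.1017 × 0.8983)/167] = 0.0295. Then Φ(0.005/0.0295 − 1.645) = 7.0%.

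Because f is the uncaptured share, hospital records reduce it. If 10 to 20% of leaks came after FU3 and records caught half of them, f would be 5 to 10% and the one-sided error 5.9 to 7.0%.

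**The case against.** **Hospital records cover much of the gap.** Outcomes {12} takes from the hospital databases every complication that leads to treatment, investigation or hospitalization. These are nearly the same events that define a relevant leak, and the trial has a single centre. Adverse events are also recorded during the study under {22}. A reader might infer that every leak after FU3 is counted as a success, but the documents do not support that: no section states such a rule, and a leak treated at the centre would probably be on file. What remains is that the database sentence sits with the secondary endpoints, carries no cut-off date, and may not reach leaks treated elsewhere. The full protocol may give a cut-off date, but the schedule in the article still has no leak assessment at week 12.

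**The endpoint wording has one sensible reading.** A reader might take the definition in {12} as status at week 12, so that a leak repaired at week 3 would be a success. The same sentence goes on to define a relevant leak as any that needs revision or another intervention, and two other sections say within 12 weeks. The cumulative reading is clearly intended, and the phrase in {12} is loose rather than a second endpoint.

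**Unblinding adds little for surgeons.** Section {17} says that surgical staff cannot be blinded, so release after FU3 tells the operating surgeon nothing new. It matters mainly for patients, ward staff and the researchers who are re-blinded after surgery. This limits that part of the point but does not remove it.

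**The size is conditional.** The missed share is assumed, and the documents give no sign that visit timing differs between arms. Both objections are correct, and the calculation needs no difference between arms.

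**Conclusion.** The point holds as a mismatch that should be reconciled. The primary endpoint runs to 12 weeks, the last scheduled leak assessment can be six weeks earlier, and unblinding is allowed from that visit. Late leaks may be missed and then scored as successes. How many is unknown, because hospital records give partial cover of unstated length.

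The direction is firm under equal under-capture: it favours non-inferiority. The size rests on the assumed 5 to 20% missed, 167 per arm and a normal approximation. On that basis the error at the margin is about 6 to 10% against a nominal 5%, or about 3 to 5.5% against 2.5% with the two-sided interval. No stated figure is wrong, and 334 and 350 stand.

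**What to change.** - In Outcomes {12}, define the primary endpoint as any qualifying leak from surgery through day 84, counted cumulatively, in line with the Abstract and {19}.
- For each patient whose FU3 falls before week 12, close the endpoint with a hospital-record check dated to day 84 and one scripted telephone question that also asks about care received elsewhere. Name both as sources for the primary endpoint.
- In {17b}, permit routine unblinding only after that closure. The existing provision for serious adverse events can stay as it is.

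If the sponsor does not want this check, the alternative is to define the endpoint as leak up to FU3 and drop the 12-week claim. Observation would then differ by up to six weeks between patients, and the report should say so.

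The cost is wording in two sections, an amendment filed with the Ethical Committee under {25}, and one short record check and call by existing staff for each patient seen before week 12. The sample size does not change.

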**Enrollment**					
Eligibility screen	X				
Informed consent	X				
Randomization		X			
**Interventions**					
Supratentorial/fossa posterior surgery		X			
Dura closure		X			
**Assessments**					
Medical history	X				
EQ-5D	X				X
RAND SF-36	X				X
MR imaging	X				X
Cost/material registration		X			
CSF leakage assessment			X	X	X
Wound healing assessment			X	X	X
Infection assessment			X	X	X
Adverse events		X	X	X	X

*FU* follow up

^a^Two days postoperative

^b^At hospital discharge

^c^Six to twelve weeks postoperative

### Participant timeline {13}

#### Screening

On the day of hospital admission (usually one day before surgery), informed consent is obtained, and the eligibility criteria are checked. Relevant medical history, medication use, vital parameters (blood pressure, temperature), and smoking and alcohol use are recorded. EQ-5D and RAND SF-36 questionnaires are completed.

#### Randomization

During surgery, the patients are randomized into the experimental (L-PRF) and control (commercially available fibrin sealant) groups.

#### Hospitalization

During their hospital stay, patients are evaluated 2 days after surgery (FU1) and on the day of discharge (FU2). The surgical site is assessed for signs of CSF leakage and/or infection. Medication administration and vital parameters are recorded.

#### Outpatient follow-up

At 6–12 weeks (FU3), the patient is seen at the outpatient department for another examination of the surgical site. CSF leakage, infection, and wound healing are assessed. Medication use is recorded, and EQ-5D and RAND SF-36 questionnaires are completed. Postoperative imaging is performed.

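### The primary endpoint runs to 12 weeks, but the last scheduled leak assessment may fall at week 6 and no dated check to week 12 closes the gap

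*Protocol article*

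**What the plan says.** The horizon of the primary endpoint is fixed at 12 weeks in three places in the protocol article:

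- Abstract, Methods/design: "The primary endpoint is postoperative CSF leakage within 12 weeks after surgery".
- Outcomes {12}, where success is "the absence of a clinically relevant CSF leak at 12 weeks after surgery". A leak is relevant if it leads to revision, another intervention, a longer stay or repeat imaging.
- Data management {19}, where the arms are to be compared on "the proportion of patients presenting with a postoperative CSF leakage within 12 weeks after surgery".

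The schedule is looser. Table 2 places leak assessment at FU1 (day 2), FU2 (discharge) and FU3, and its footnote dates FU3 as "Six to twelve weeks postoperative". The participant timeline says the same: "At 6–12 weeks (FU3), the patient is seen at the outpatient department for another examination of the surgical site". The caption of Fig. 2 shows that this is the only outpatient contact: "One outpatient follow-up is done between 6 and 12 weeks postop (FU3"). Outcomes {12} ties assessment to visits: "The outcomes will be assessed at five study visits within a timeframe of twelve postoperative weeks".

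Four other statements bear on the point:

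- Outcomes {12} draws complications, CSF leakage among them, from the hospital databases.
- The retention section {18b} provides a telephone contact for missed or out-of-window visits, for completing the questionnaires.
- Section {17b} permits unblinding once FU3 is complete.
- Section {20c} expects no missing primary data.

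**The concern.** A patient who attends FU3 at week 6 has followed the schedule fully, yet nothing is scheduled for the remaining six weeks of the endpoint period. This concerns patients who attend as planned, not those lost to follow-up.

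Success is the absence of a leak and no primary data are expected to be missing, so a leak that arises after FU3 and is not found would by default be analysed as a success. If the same share of leaks is lost in both arms, the observed risk difference is the true difference multiplied by the share captured. The margin is an absolute 0.05 and does not shrink with it, so the error favours a conclusion of non-inferiority.

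Because unblinding is allowed from FU3, a leak that comes to light between FU3 and week 12 could also be judged with the allocation known, inside the endpoint period.

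**Working it through.** **1. The plan's own figure.** Inputs from Sample size {14}: success 93.7% (control) and 95% (L-PRF), margin 0.05, one-sided alpha 0.05, power 80%.

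n per arm = (0.937×0.063 + 0.95×0.05) × (1.645 + 0.842)² / (0.05 + 0.013)² = (0.0590 + 0.0475) × 6.183 / 0.003969 = 165.9

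This gives 166 per arm and 332 in total, against 334 stated, so the figure is reproduced to within two patients. Nothing below changes it.

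**2. The window.** The largest part of the endpoint period without a scheduled leak assessment is (12 − 6)/12 = 50%. This is a share of time, not of leaks.

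**3. Share of leaks unseen.** Let L be the share of all leaks that arise after week 6, f the fraction of those that fall after the patient's own FU3, and d the fraction of those that the databases find. Then the unseen share is

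u = L × f × (1 − d)

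The documents give none of the three, so all are assumptions. For illustration, L is 5–20%, and f is 0.5 if visits and late leaks are both spread evenly over weeks 6–12, or 1 if every visit falls at week 6.

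| L | f | d | u |
|---|---|---|---|
| 5% | 0.5 | 0 | 2.5% |
| 20% | 0.5 | 0.5 | 5% |
| 20% | 0.5 | 0 | 10% |
| 20% | 1 | 0 | 20% |

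**4. Effect on false non-inferiority.** Take true leak rates at the margin: 6.3% in control (1 − 0.937) and 11.3% with L-PRF (6.3% + 5 points). With a share u unseen in both arms, the observed rates are 6.3%×(1 − u) and 11.3%×(1 − u), and the observed difference is 5.0×(1 − u) points. The probability of passing is the exact sum over both binomial distributions, 175 per arm, of outcomes whose Wald bound lies inside 0.05.

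| Unseen u | Observed difference | One-sided 0.05 | Two-sided 95% interval |
|---|---|---|---|
| 0 | 5.0 points | 5.5% | 2.8% |
| 2.5% | 4.875 points | 6.0% | 3.0% |
| 5% | 4.75 points | 6.5% | 3.4% |
| 10% | 4.5 points | 7.8% | 4.1% |
| 20% | 4.0 points | 11.0% | 6.2% |

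Both columns are shown because Sample size {14} uses a one-sided 0.05, while Statistical methods {20a} reports a two-sided 95% interval. The first row lies above 5% and 2.5% because the Wald bound is slightly liberal at these rates; the effect of under-capture is the change from that row. With 167 per arm the picture is the same: 5.7%, 8.0% and 11.2% at u = 0, 10% and 20% for one-sided 0.05.

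**The case against.** The strongest reply is that a clinically relevant leak is defined by its consequences (revision, puncture, longer stay, imaging), and these leave a hospital record. All patients are operated on at one centre, complications including CSF leakage are taken from that hospital's databases, and no cut-off at FU3 is stated. The date of data extraction is also a detail that an article may leave to the full protocol.

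Much of this stands. A reader might infer that weeks 6–12 are simply unobserved. The documents do not support that: what is missing is a scheduled assessment, and some late leaks would probably be found. It does not close the gap, however. The database sentence sits with the secondary endpoints, is not tied to week 12, and may not reach care given elsewhere. Data collection {18a} names hospitalization reports and outpatient follow-up as the postoperative sources, with none after FU3. The telephone contact in {18b} is for questionnaires, with no leak question stated.

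Three further inferences go too far:

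- That many patients are affected: the spread of FU3 dates is not given, and if most visits fall near week 12 the gap is small.
- That half the window means half the leaks: no leak timing is given.
- That the plan has a rule scoring unseen leaks as successes: this follows by default from the endpoint definition and the expectation of no missing data, but is not written.

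It is also fair that, with the two-sided 95% interval, every scenario up to 10% unseen stays at or below 4.1%, under the 5% level used for the sample size.

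**Conclusion.** The mismatch is real and rests on the protocol's own text: a fixed 12-week endpoint is served by a last scheduled leak assessment that may come at week 6. The direction, towards non-inferiority, follows if under-capture is equal in both arms.

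The size cannot be determined from the documents. For 2.5–10% of leaks unseen after any database capture, the increase in false non-inferiority is 0.5 to 2.3 percentage points at one-sided 0.05 (5.5% to 6.0–7.8%) and 0.2 to 1.3 points with the two-sided 95% interval (2.8% to 3.0–4.1%). The 20% case (11.0% or 6.2%) is extreme: in the illustration it needs one leak in five to arise after week 6, every visit to fall at week 6, and the databases to find none of the later leaks.

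Confidence is high in the mismatch and low in the size of the bias. The point is worth acting on because it touches the primary endpoint of a non-inferiority trial and is cheap to close.

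**What to change.** - **Ascertainment.** State that leak status is established to day 84 for every patient by a dated search of the hospital record. For patients whose FU3 came earlier, add one scripted question on leak, revision, puncture or admission at any hospital. For patients already past week 12 (recruitment began in January 2020), only the record search and, where possible, a retrospective question can be done.
- **Blinding.** Keep the leak assessor blinded until day 84 rather than until FU3, leaving the existing provision for related serious adverse events as it is.
- **Data and analysis.** Record the date of leak and the date last known leak-free, state how a patient with no information after an early FU3 is classified, and add a sensitivity analysis of 12-week cumulative incidence.

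Shortening the endpoint to 6 weeks is not recommended: it would discard leaks seen between week 6 and FU3.

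The cost is a short amendment, the two dates in the case report form, a record search to day 84, and one call for each patient with an early FU3, all within reach of the existing study coordinator. The sample size of 334 (350 enrolled) is unchanged.
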